## Abstract

**Introduction:**

Major surgery accounts for a substantial proportion of health service activity, due not only to the primary procedure, but the longer-term health implications of poor short-term outcome. Data from small studies or from outside the UK indicate that rates of complications and failure to rescue vary between hospitals, as does compliance with best practice processes. Within the UK, there is currently no system for monitoring postoperative complications (other than short-term mortality) in major non-cardiac surgery. Further, there is variation between national audit programmes, in the emphasis placed on quality assurance versus quality improvement, and therefore the principles of measurement and reporting which are used to design such programmes.

**Methods and analysis:**

The PQIP patient study is a multi-centre prospective cohort study which recruits patients undergoing major surgery. Patient provide informed consent and contribute baseline and outcome data from their perspective using a suite of patient-reported outcome tools. Research and clinical staff complete data on patient risk factors and outcomes in-hospital, including two measures of complications. Longer-term outcome data are collected through patient feedback and linkage to national administrative datasets (mortality and readmissions). As well as providing a uniquely granular dataset for research, PQIP provides feedback to participating sites on their compliance with evidence-based processes and their patients’ outcomes, with the aim of supporting local quality improvement.

**Ethics and dissemination:**

Ethical approval has been granted by the Health Research Authority in the UK. Dissemination of interim findings (non-inferential) will form a part of the improvement methodology and will be provided to participating centres at regular intervals, including near-real time feedback of key process measures. Inferential analyses will be published in the peer-reviewed literature, supported by a comprehensive multi-modal communications strategy including to patients, policy makers and academic audiences as well as clinicians.

## Strengths and limitations of this study

### Strengths

The largest observational study of patients undergoing major surgery in the UK National Health Service.The first national effort to measure and report risk-adjusted complications, patient-reported outcome and mortality rates for patients undergoing major surgery in the UK.

### Limitations

The requirement for patient consent means that the sample may be biased. While this is of less importance for process measures which will be used to evaluate care quality, it is relevant when considering outcomes. We will mitigate this risk through comparison of the PQIP population to the total sample of patients undergoing PQIP included procedures using Hospital Episode Statistics (HES) data. This will enable us to undertake sensitivity analyses which will demonstrate what (if any) biases there are in our sampling.Similarly, our ambition to enable as many hospitals as possible to participate irrespective of local resourcing, means that some hospitals will attempt to recruit all patients who are potentially eligible, and some only a sample. We will again try to mitigate this risk through encouraging hospitals to recruit a random sample of patients and will compare the PQIP sample against the HES-defined population at local level as well.

## Introduction

Approximately 1.5 million major surgical procedures are carried out in the UK National Health Service per year at a cost of around £5 billion (Abbott et al. 2017); globally, surgical caseload substantially exceeds 300 million procedures per annum (Weiser et al. 2015). International estimates of death within 30 days of planned (elective or expedited) surgery vary, but it is acknowledged to be relatively uncommon in high income nations (around 0.6% to 4% depending on the study design, health system and population characteristics) (Abbott et al. 2017; Pearse et al. 2012; Ghaferi et al. 2009). However, there are several reasons why these low estimates of short-term mortality may provide false reassurance about the quality of perioperative care and the potential health and economic burden on patients and society. First, the incidence of major or prolonged postoperative morbidity is at least ten times higher than short-term mortality (Moonesinghe et al. 2014). This is important, because major morbidity contributes to increased length of hospital stay and associated increased cost of healthcare. Second, US data have shown wide variation in risk-adjusted morbidity and failure-to-rescue rates between the sample of healthcare providers who voluntarily participate in the American College of Surgeons’ National Surgical Quality Improvement Program (ACS-NSQIP), suggesting that at least some of these poor short-term outcomes could be avoidable (Ghaferi et al. 2009; Ghaferi et al. 2009). However, the lack of a unified national system for measuring complications across different types of major surgery in the NHS means that it is currently not possible to ascertain if the UK has the same problem. Third, a consistent finding across different procedures, populations and healthcare systems is the independent association between short-term postoperative complications and reduced longer-term survival (Moonesinghe et al. 2014; Khuri et al. 2005; Toner and Hamilton 2013). It therefore follows, that the outcome of surgery should not be defined entirely by short-term survivorship. Longer-term and additional patient-centred outcomes such as quality of life or disability-free survival are increasingly viewed as important measures of perioperative ‘success’ by both clinicians and patients, but there is comparatively little high quality data on these outcomes (Boney et al. 2016; Myles et al. 2016). This is particularly important given the evolving demographics of the surgical population (increasing age and multi-morbidity) and the increased number of surgical options available for previously untreatable conditions. There is also a recognition that not all interventions are in the best interests of patients, and sometimes less invasive approaches may lead to better outcomes and fewer adverse events (Skou et al. 2015; Kise et al. 2016). Thus, understanding the full implications of a surgical intervention is critical to supporting high quality patient care and shared decision making.

Beyond understanding these issues more clearly, there is also a need to measure and improve structures and processes associated with perioperative care, so that outcomes may also improve. Numerous national audit and quality improvement initiatives are already operational in the UK, ranging from short-term evaluations of specific clinical areas (e.g. National Confidential Enquiry into Patient Outcome and Death (NCEPOD)) to longer-term continuous national registries and audits (e.g. the National Joint Registry or the National Emergency Laparotomy Audit (NELA)). While these audits are important for national monitoring and quality assurance, the use of data for improvement by clinical teams is variable, despite basic reports of local data being available for review immediately upon electronic data entry. It is common that local teams wait for national reports to be published to take action on their local performance, and the lag time between data collection and publication of national results can therefore be a barrier to quality improvement (QI). Thus, the use of data to drive local QI activity in these different programmes varies considerably, both because of the variation in the methodology of the programme (e.g. ACS-NSQIP provides only annual reporting) and because of variation in the capacity and capability of clinical teams to review quality data, even if available to them prospectively and continuously, driven by culture, resource availability and clinician engagement (Allwood 2014).

The PQIP patient study attempts to address these areas of need through a comprehensive national programme of data collection and feedback, incorporating a multi-level complex intervention aimed at supporting the use of data for improvement at local level. We describe here the protocol for the data collection and feedback. The complex intervention will be described and evaluated in separate papers.

## Methods

### Main study design

Prospective cohort study of patients undergoing major surgery in NHS hospitals. Observational study at patient level; interventional action research study using time-series analysis at hospital level.

### Aims

To measure processes of care and outcome in patients undergoing major surgery in the UK NHS.To create a national resource for the collection, management and analysis of high-quality perioperative data, to support collaborative research and efficient study design.To implement and evaluate a complex intervention aiming to enhance the use of data for improvement by clinical teams

### Objectives

To comprehensively measure and report structures, processes and risk-adjusted complications, patient-reported outcome and mortality rates after major surgeryTo evaluate the relationships between structures, processes and outcomes after major surgeryTo develop bespoke, regularly updated and non-proprietary risk models for the purposes of case-mix adjustment and perioperative risk prediction for different outcomesTo support local quality improvement through feedback of data to clinicians and managers using near-real-time feedback and regular comprehensive reporting.To develop and evaluate the effectiveness of a theoretically underpinned complex intervention involving novel methods of data feedback, analysis and support mechanisms to aid local improvement initiatives.To support the development and delivery of collaborative nested studies.

### Research questions

What is the level of compliance with evidence-based structures and processes for patients undergoing major surgery?What are the rates of complications, failure to rescue (FTR), short- and long- term mortality in patients undergoing major planned surgery in NHS hospitals?How do the rates of adverse outcomes vary over time and between institutions?Are there structural or process related predictors of these adverse outcomes?What is the relationship between different measures of postoperative outcomes (e.g. different measures of morbidity; short and longer-term outcomes, health-related quality of life and disability)?What is the validity and predictive performance of previously published risk prediction models for different perioperative outcomes in the PQIP population?Can existing risk models be improved, or more parsimonious versions developed to support temporally responsive risk adjustment and clinically useful risk evaluation?How representative is the sample of patients recruited to PQIP of the total cohort of patients undergoing potentially eligible procedures in PQIP hospitals?Is there an outcome benefit to hospital and/or patient involvement in PQIP which can be differentiated from secular variation?Can quality of care be improved through a theoretically underpinned complex intervention supporting the use of data for improvement at local level, and do patient outcomes also improve?

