### Evaluating sample validity (RQ8)

One of the objectives of PQIP is to measure and report processes and outcomes from surgery for the purposes of quality improvement. While it is widely accepted that data from a non-random sample of patients within an institution may provide important information about reliability of processes and systems (Peden and Moonesinghe 2016), sampling of patient outcomes should be statistically and conceptually robust so as not to provide biased estimates. Clinical trials and cohort studies which have specific inclusion and exclusion criteria, or which require patient consent, can be criticised as non-representative (and therefore the findings are of limited generalisability) (Deaton and Cartwright 2018). A potential solution to this is to use administrative data to evaluate outcomes; however, in the UK, such data are limited to mortality, hospital readmission and length of stay.

We will address these issues through an evaluation of our sampling strategy using administrative data from Hospital Episode Statistics (HES). For included procedures, an anonymised extract of HES data will be requested from NHS Digital for each hospital. This will enable us to conduct sensitivity analyses comparing patient characteristics (for example age, comorbidity, socioeconomic status using the Index of Multiple Deprivation) and outcomes (mortality, hospital readmission, length of hospital stay) between patients included in PQIP and those who are not. We will do this at individual hospital level and at aggregate (national) level.

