### Evaluating impact of PQIP (RQ9)

We will compare risk-adjusted patient outcomes which are available from administrative data (e.g. mortality, length of stay, readmission to hospital, ‘days alive and out of hospital’ at 30 and 90 days and one year after surgery (Moonesinghe et al. 2019)) in hospitals and patients who are enrolled in PQIP and those who are not. Temporal trends will be analysed using a difference in differences approach. In order to avoid bias associated with different hospital types which may affect patient outcomes irrespective of involvement with PQIP, we will apply coarsened exact matching (Iacus et al. 2012; Bonfrer et al. 2018), matching PQIP and non-PQIP hospitals using pooled data from organisational surveys conducted by the Health Services Research Centre for PQIP and other studies (e.g. SNAP2-EPICCS (Moonesinghe et al. 2017)and the National Emergency Laparotomy Audit (National 2014)) as well as open-access external sources such as NHS England and Department of Health datasets.

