## Discussion

PQIP has now been running for 4 years, and was paused for approximately one year during the Covid pandemic, both because elective surgery activity reduced substantially, and because clinical and research teams were diverted to support the emergency response. Review of data collected to that point and discussion with clinical teams has found that the random sampling approach was largely infeasible at hospital level. Therefore, a convenience sampling approach has been adopted by most sites. This further underlines the importance of our planned analyses to evaluate risk of bias in our patient selection and our results.

This also highlighted another challenge with our approach: the direct cost of participation in the study. Hospitals are incentivised to take part because the PQIP patient study is registered on the National Institute for Health Research’s portfolio of approved studies: therefore, sites are financially rewarded for recruiting patients. However, the costs of data collection and entry must be covered locally, and this is a significant challenge, which has limited both site participation and the number of patients recruited per site. Nonetheless, over 126 hospitals have taken part in the PQIP patient study so far, and over 35,000 patients have been recruited.

PQIP has also successfully collaborated with another research team to facilitate an NIHR funded randomised controlled trial to use the PQIP data collection platform and co-recruit into both studies (https://www.journalslibrary.nihr.ac.uk/programmes/hta/NIHR130573/#/) This approach to efficient trial design should bring benefit to patients, clinicians, researchers and provide excellent value for money.

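### As worded, RQ8 checks representativeness only against PQIP hospitals, aim 1 and RQ2 target the NHS, and no specified analysis isolates the selection of hospitals into PQIP

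*Protocol article*

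**What the plan says.** All references are to the protocol article.

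- **Target.** The first aim is "To measure processes of care and outcome in patients undergoing major surgery in the UK NHS". RQ2 asks for rates of complications, failure to rescue and mortality "in patients undergoing major planned surgery in NHS hospitals".
- **Check on representativeness.** RQ8 is the only research question on this. It asks: "How representative is the sample of patients recruited to PQIP of the total cohort of patients undergoing potentially eligible procedures in PQIP hospitals".
- **Limitations.** The stated mitigation is "comparison of the PQIP population to the total sample of patients undergoing PQIP included procedures" using HES, with a local comparison in addition. No restriction to PQIP hospitals appears there.
- **Evaluating sample validity (RQ8).** The data source is described thus: "For included procedures, an anonymised extract of HES data will be requested from NHS Digital for each hospital". Patients in PQIP are to be compared with patients not in PQIP, hospital by hospital and nationally in aggregate. The section also says that UK administrative data give only mortality, readmission and length of stay.
- **Evaluating impact of PQIP (RQ9).** Administrative outcomes are compared "in hospitals and patients who are enrolled in PQIP and those who are not", using difference in differences and coarsened exact matching of hospitals.
- **Discussion.** Data collection costs fall on the hospital, and "this is a significant challenge, which has limited both site participation and the number of patients recruited per site".

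**The concern.** There are two layers of selection between the NHS and the PQIP dataset. Hospitals decide whether to take part, and patients within those hospitals are then sampled and asked for consent. RQ2 needs both layers to be harmless, or at least measured. RQ8 as worded addresses the second only.

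The article itself supplies the ingredients for bias at the first layer. It says that cost restricted which sites joined. In motivating the RQ9 matching, it also accepts that hospital type may affect outcomes whether or not a hospital is in PQIP.

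At stake is what the RQ2 rates can be said to describe. A favourable RQ8 answer could be offered in support of NHS-wide rates although it says nothing about hospitals outside the programme. Unlike sampling error, this bias does not shrink as recruitment moves towards 70,000.

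**Working it through.** The article gives no figure for hospital selection, so there is nothing to reproduce. The check is first textual, then illustrative.

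**1. Who is in the reference population?**

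| Place | Population named |
|---|---|
| Aim 1 | UK NHS |
| RQ2 | NHS hospitals |
| RQ8 | PQIP hospitals |
| Limitations | everyone having an included procedure; hospitals not specified |
| RQ8 analysis | patients in PQIP against those outside it, by hospital and nationally; hospitals in the HES extract not specified |

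The RQ8 question and its own analysis section can be read together only by choosing what the national comparison covers.

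**2. What each reading would deliver.** For an administrative outcome, let r1 be the rate in PQIP patients, r2 the rate in other eligible patients at PQIP hospitals, and r3 the rate in eligible patients at non-PQIP hospitals. Let w be the share of all non-PQIP patients who were treated at PQIP hospitals.

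- *National means PQIP sites pooled:* the contrast is r1 − r2. Hospital selection does not enter it.
- *National means all hospitals:* the contrast is r1 − [w·r2 + (1 − w)·r3] = (r1 − r2) + (1 − w)(r2 − r3). It adds patient selection to a weighted hospital gap, and the two can offset each other. The hospital-level comparison estimates r1 − r2, so the hospital part could be inferred by comparing the two results. The article does not say that this will be done.

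**3. Does RQ9 fill the gap?** Difference in differences cancels a constant difference in level between PQIP and non-PQIP hospitals. Matching on hospital characteristics reduces that difference further. A null RQ9 result is therefore compatible with a large r2 − r3. The purpose is programme effect, and no unmatched gap is tied to RQ2.

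**4. Illustrative size.** Let p be the rate in PQIP hospitals, f the share of eligible caseload in non-PQIP hospitals, and RR the rate there relative to PQIP hospitals. Then the NHS rate is p[1 + f(RR − 1)], and

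bias (PQIP minus NHS) = −f·p·(RR − 1).

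Inputs: p = 0.6% and 4%, the ends of the international range for death within 30 days of planned surgery in the Introduction. n is 35,000 (the Discussion reports more than this recruited) and 70,000 (the target). f = 10% to 50% and RR = 0.9 to 1.25 are **assumptions**. The article says that more than 126 hospitals have taken part but not how many are eligible, so f cannot be calculated.

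Sampling half-width = 1.96·√[p(1 − p)/n], simple random sampling, no clustering:

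| p | n = 35,000 | n = 70,000 |
|---|---|---|
| 0.6% | 0.081 points | 0.057 points |
| 4% | 0.205 points | 0.145 points |

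Bias in percentage points:

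| f | RR | p = 0.6% | p = 4% |
|---|---|---|---|
| 10% | 1.10 | −0.006 | −0.04 |
| 30% | 1.10 | −0.018 | −0.12 |
| 30% | 1.25 | −0.045 | −0.30 |
| 50% | 0.90 | +0.030 | +0.20 |
| 50% | 1.25 | −0.075 | −0.50 |

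Bias equals the half-width when f·\|RR − 1\| = half-width/p. At n = 70,000 this is 0.057/0.6 = 0.095 for the lower rate and 0.145/4 = 0.036 for the higher. At p = 0.6% only the most extreme row passes it. At p = 4% the last three rows do.

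**5. Outcomes that HES cannot reach.** The primary outcome is POMS morbidity on day seven. Failure to rescue uses Clavien-Dindo grade II or above as its definition of a complication. Neither these nor complication rates are in the administrative data the article describes, so r3 cannot be observed for them on either reading.

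**The case against.** The strongest reply is that the single sentence of RQ8 is not the whole plan. The Limitations promise a comparison with all patients having the included procedures and mention the local comparison as an addition, which suggests that the first is wider. The RQ8 analysis works at two levels, and if the national one covers all hospitals, the pair of results shows hospital selection indirectly. RQ9 draws on outcomes in non-enrolled hospitals, and difference in differences needs them for a period before participation. An article also condenses a full protocol, which may define the extract. The Discussion is open about limited site participation and convenience sampling.

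Much of this stands. A reader might infer that representativeness is examined only inside PQIP hospitals and that hospital selection is never estimated. The article does not support that, because the wider wording may reach other hospitals. A reader might also infer that the bias is several times the study's stated precision. No precision is stated: the sample size section gives a recruitment target only. The half-widths above ignore clustering by hospital, which would normally widen them. That the rates would be taken as NHS-wide is likewise an inference, though aim 1 and RQ2 invite it.

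What the reply does not remove is the conflict itself. RQ8's reference population is written into this article and differs from that of aim 1 and RQ2, so it is not a detail left to another document. On the generous reading, the hospital component is still not named as a quantity to report, and RQ9 is built to eliminate it.

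**Conclusion.** The point holds as a mismatch of scope with a consequence for RQ2. The article names different reference populations in different places, acknowledges that site participation was restricted, and specifies no analysis that isolates the resulting bias in the RQ2 rates.

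Its size is unknown. Under the assumptions shown, bias in mortality runs from +0.03 to −0.075 points at a 0.6% rate and from +0.20 to −0.50 points at 4%. It exceeds sampling error only for the larger assumed values of caseload share and rate ratio. These figures show that the question is worth answering; they do not show that the bias is present.

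For morbidity, complications and failure to rescue, the planned administrative data cannot test the step from participating hospitals to the NHS. The wording of the claim is the only safeguard for those outcomes.

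**What to change.** 1. **Align the reference population** in the Limitations, RQ8 and the RQ8 analysis section: eligible patients in all NHS hospitals performing the included procedures. State explicitly that the HES extract covers non-PQIP hospitals.
2. **Report two contrasts separately** in the RQ8 analysis, for mortality, readmission and length of stay:
   - (a) PQIP patients against other eligible patients in PQIP hospitals, as patient selection;
   - (b) all eligible patients in PQIP hospitals against those in non-PQIP hospitals, unmatched and in periods before joining, as hospital selection. Using earlier periods keeps any effect of PQIP out of the selection estimate.
3. **Label the rates.** Give RQ2 morbidity, complication and failure-to-rescue rates as 'in participating hospitals'. Use the same label for the administrative-outcome rates unless (b) proves small.
4. If an illustrative bias is quoted, compare it with a sampling half-width and state the assumed caseload share and rate ratio.

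The cost is revised wording in three places, one further contrast, and a more modest label on the national rates. RQ9 needs administrative outcomes from non-PQIP hospitals in any case, although the article does not confirm that the extract described for RQ8 includes them.
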